### The YoPA co-creation protocol

We will start with collaboratively developing one overall YoPA co-creation protocol together with the local researchers from all four study sites. The YoPA co-creation protocol aims at high-quality co-creation (i) based on state-of-the-art science-based and practice-based evidence and theory; (ii) tailored to the local context, including the local needs and preferences of adolescents; (iii) acceptable and feasible for local stakeholders responsible for implementation. This protocol ensures a systematic, evidence-based and theory-based application of co-creation leaving space for adaptation to each local context. The overall co-creation protocol will include building an infrastructure for continuous capacity building for adolescents, as well as local stakeholders to stimulate participatory thinking, active engagement, equal collaboration and training in research and other relevant skills. This protocol will describe how to apply youth-centred co-creation including recruitment and all methods for capacity building and peer research. We will organise training for local facilitators of the youth-centred co-creation process, as well as for key stakeholders to stimulate their active contribution to the co-creation process. Academic researchers bring in their state-of-the-art scientific knowledge and experience with developing evidence-based interventions while adolescent researchers bring in their lived experience. In YoPA, we aim to develop academic and adolescent researchers’ collective agency, by building their capacities for collaboration, peer-research and intervention development. Collaborating with other key stakeholders from multiple sectors in the system will gain a deeper understanding of the complex system and thereby contribute to more holistic and contextually relevant interventions.

### Engaging local YoPA communities

We will engage four local co-creation communities, two communities in minority countries (Denmark and the Netherlands) and two in majority countries (Nigeria and South Africa). In each community, a dynamic group of 15–20 adolescents will be recruited to participate as co-researchers in local co-creation groups facilitated by an academic researcher. Recruitment will take place through diverse channels and settings including schools, local community centres, youth clubs, religious meeting places and other relevant settings where adolescents with diverse backgrounds meet. We will use a purposive sampling method tailored to each local context (eg, social media, flyers) in collaboration with local non-governmental organisations and other community stakeholders. By ensuring safe spaces, skilled facilitators and capacity building, adolescents in local co-creation groups will be encouraged to actively engage and contribute to the co-creation process. We will conduct stakeholder analyses to identify and recruit other key stakeholders (eg, existing community-based organisations and local authorities with a shared agenda), who will be invited to actively contribute to the co-creation process by joining meetings of the local co-creation groups. The co-creation process will take place during regular participatory meetings with adolescents facilitated by an academic researcher over the course of 3 years. To maximise chances of sustained commitment, we will collaborate with local community groups organised around health advocacy, sports, music or social activity. We will emphasise social inclusion by involving adolescents of different genders and backgrounds.

### Mapping the local context

To ensure YoPA will address questions and outcomes that are most relevant to the local communities, thereby promoting uptake and sustainability of the interventions, we will start with mapping the local context by an audit and environmental scan of selected communities to identify local needs and priorities using various state-of-the-art participatory methods, for example, photovoice,^73^ community mapping^74^ and neighbourhood walks.^75^ To explore the local communities at multiple levels, that is, including linkages, relationships, feedback loops and interactions, we will use systems methods such as group model building^76^ and social network analysis.^77^ We will use Causal Loop Diagrams as a tool to explore the multiple, interacting feedback loops operating in the existing local system. Such Causal Loop Diagrams create a dynamic, holistic view of the existing system, including intended and unintended potential consequences, and the ways in which interventions in one setting, such as home or school, might be influenced by the interactions with other settings, such as macroeconomic and urban systems, for example, public space.^14 78^ In bringing together key stakeholders (locally, nationally or internationally) to understand the root causes of unhealthy movement behaviours, a systems approach enables each stakeholder to see where they fit within a bigger picture.^17^ To ensure results align with the perspectives of the wider community, emerging findings will be shared with community representatives for them to critically examine and contribute. For this step, we may use structured interview matrix^79^—a community-based research method that allows large groups (up to 40 participants) to discuss directions for future developments and priorities in an iterative, structured and transparent process—and multicriteria decision-making matrices,^80^ to weigh all collected data in a transparent way. Each local system map will include an agreed set of priorities for holistic, systemic interventions in each local community.

### Selection, tailoring and implementing evidence-informed interventions

Based on the local system maps, the best matching evidence-based interventions will be selected from (i) local youth-led knowledge, (ii) ISPAH’s eight investments that work for physical activity; (iii) literature reviews conducted by the academic researchers and (iv) other relevant (local) literature and databases including evidence-based interventions. For each of the selected interventions, we will develop an intervention theory to help identify key working mechanisms, salient context conditions and relevant additional outcomes. The intervention theories will be grounded in existing evidence and empirically tested in the local contexts. The selected interventions will be aligned with local priorities and existing strategic plans where possible, based on the local system maps and meetings with key stakeholders, to obtain support and ensure feasibility, sustainability and resources for the implementation. Key considerations for our settings are safety and crime (especially for adolescent girls), limited infrastructure and resources and transport challenges.

### Evaluate interventions using the SUPER-AIM framework

The YoPA evaluation will take a systems perspective, aiming to evaluate a range of outcomes, associated processes and their dynamic inter-relationships using interrupted time series methods as one of the strongest quasi-experimental research designs.^81^
Table 1 describes the specific outcomes, samples and proposed methods for each component of our SUPER-AIM framework. Together with the local co-creation communities, we will select and/or modify the most appropriate methods that allow the collection of quantitative and qualitative data at all system levels, including measures of the process and outcomes of the co-creation and implementation of interventions. Process data will be collected continuously from the start of the co-creation process. Outcome data will be collected before and 6 months after implementation of interventions as well 6–12 months later depending on the local situation. For the outcome evaluation, we aim to recruit 200–250 adolescents in each local community. Training of (adolescent) data collectors for collecting data in the four communities will follow the ‘train-the-trainer’ principle: one meeting will be organised to train the researchers responsible for data collection in their country, who will subsequently train local (adolescent) data collectors. As there is a lack of evidence on the application of youth-centred co-creation in vulnerable settings in both majority and minority countries, we aim to better understand the mechanisms underlying co-creation through personal and collective agency in each of the settings with the help of a realist evaluation.^82^ Next to evaluating the outcomes of interventions, realist evaluation aims to understand why and how specific outcomes were reached in each setting and thus contributes to building the theory base on why interventions work (or not), and for whom, in a range of settings. Collaborating and sharing experiences across the four co-creation sites through online meetings, exchanges and joint analyses may help to generalise findings.

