**Methods and analysis:**

In diverse urban environments in Denmark, the Netherlands, Nigeria and South Africa, we will engage a dynamic group of 15–20 adolescents (12–19 years) growing up in vulnerable life situations and other key stakeholders (eg, policy makers, urban planners, community leaders) in local co-creation communities. Together with academic researchers and local stakeholders, adolescents will take a leading role in mapping the local system; tailoring; implementing and evaluating interventions during participatory meetings over the course of 3 years. YoPA applies a participatory mixed methods design guided by a novel Systems, User perspectives, Participatory co-creation process, Effects, Reach, Adoption, Implementation and Maintenance framework assessing: (i) the local systems, (ii) user perspectives, (iii) the participatory co-creation process, (iv) effects, (v) reach, (vi) adoption, (vii) implementation and (viii) maintenance of interventions. Through a realist evaluation, YoPA will explore why and how specific outcomes were reached (or not) in each setting (n=800–1000 adolescents in total).

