### Analyses

Data collected by adolescent-researchers throughout the co-creation process will be analysed using the best available and accessible techniques with options for facilitated co-researcher involvement. The selected methods should be engaging to the co-researchers, suited to answering their research questions and supported by a skilled academic researcher. Following data cleaning and data processing, we will analyse the outcomes of the implemented interventions, as well as the dynamics underlying these, combining and comparing data from the four study sites. We will conduct analyses of a combination of quantitative (eg, sensor-based behavioural data) as well as qualitative (eg, interviews and user-generated data) data.^83^ Quantitative data will be analysed using appropriate techniques (eg, multilevel modelling appropriate for individual-level data nested within communities). Qualitative data will be summarised and subsequently analysed using open and axial coding by two independent researchers. Intersectionality references the critical insight that race, class, gender, sexuality, ethnicity, nation, ability and age operate not as unitary, mutually exclusive entities, but as reciprocally constructing phenomena that in turn shape complex social and health inequalities.^84^ In both quantitative and qualitative analyses, we will apply different kinds of intersectional analyses including relevant categories such as gender, age, education and ethnicity.

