A better understanding of how culture and structure impacts the co-creation process and interventions implemented in the four selected communities in YoPA benefits knowledge exchange between the different settings. Furthermore, YoPA goes beyond addressing a research gap in physical activity and health research in sub-Saharan Africa; it takes an approach to considering context in a robust and meaningful way that fully accounts for competing priorities in African settings.^20^ Currently, there is a lack of systematic and practical protocols guiding the application of co-creation for tailoring evidence-informed interventions to specific contexts, and subsequently evaluating them together with adolescents and other key stakeholders. To fill this gap, we will develop a YoPA toolbox, making all materials and training on the youth-centred co-creation for tailoring and implementation of evidence-informed interventions available through the YoPA website (yopa-project.eu), both during its development and its final form. Once results from the process, outcome and realist evaluations start to come in, more formalised guidelines for the use of the toolbox, as well as policy recommendations for the implementation of similar co-creation processes will be developed and become part of the toolbox, targeted at researchers, public health and urban planning practitioners, local authorities, policy makers, grassroots/community-based organisations and citizens.

Limitations of our study could be the lack of a controlled design and the challenge to instigate and measure sustainable system change as this cannot be externally directed, but occurs as a result of the self-organising interactions and relationships within the system. The complexity of the public health problem and context-specific approach prohibit a randomised controlled trial design. Instead, in YoPA we focus on identifying working mechanisms and detailed documentation using a mixed methods design.

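### For the outcomes measured in waves, the schedule cannot support an interrupted time series, so the stated design strength does not apply to them

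*Protocol article*

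**What the plan says.** In the protocol article, the section on evaluating interventions with the SUPER-AIM framework states that outcomes, processes and their inter-relationships will be evaluated "using interrupted time series methods as one of the strongest quasi-experimental research designs". The same paragraph sets two collection schedules:

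- For process measures: "Process data will be collected continuously from the start of the co-creation process".
- For outcomes: "Outcome data will be collected before and 6 months after implementation of interventions as well 6–12 months later depending on the local situation".

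On the outcome sample it says "we aim to recruit 200–250 adolescents in each local community", and the abstract gives "n=800–1000 adolescents in total".

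Table 1 lists the Effects outcomes as well-being, personal and collective agency, and 24-hour movement behaviours. It adds no further pre-implementation wave for any of them. The Discussion concedes: "Limitations of our study could be the lack of a controlled design". It does not mention the absence of a pre-implementation series.

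**The concern.** An interrupted time series earns its standing among uncontrolled designs in one way. It estimates the course of the outcome before the intervention from several measurements, projects that course forward, and compares it with what is then observed. With a single earlier measurement there is nothing to project.

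This matters here because the introductory section on Challenge 1 says that physical activity declines and screen time increases during adolescence. Without a control group, an estimated pre-trend would be the design's protection against reading such drift as an effect, or against missing an effect that the drift masks. If the label stands, readers will give the Effects results a causal weight that the schedule cannot supply.

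**Working it through.** **Inputs from the article.** Four communities (section on engaging local communities); 200–250 adolescents in each; outcome occasions before implementation, at 6 months, and 6–12 months after that, so the last falls at 12 to 18 months; no control group.

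**Assumption.** The baseline lead time is not given, so I take it as 1 month before implementation. The identification result does not depend on this value.

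**The plan's own figure.** 4 × 200 = 800 and 4 × 250 = 1000, which agrees with the stated total.

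**Step 1: the full segmented model.** With t in months from implementation and P = 1 after it:

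E(Y) = b0 + b1·t + b2·P + b3·P·t

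Here b1 is the pre-implementation trend, b2 the level change and b3 the slope change. The three wave means are:

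- t = −1: m0 = b0 − b1
- t = 6: m1 = b0 + 6b1 + b2 + 6b3
- t = 12: m2 = b0 + 12b1 + b2 + 12b3

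There are three equations for four unknowns. Adding c to b0 and b1, and subtracting c from b2 and b3, leaves every mean unchanged:

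- m0 changes by c − c = 0
- m1 changes by c + 6c − c − 6c = 0
- m2 changes by c + 12c − c − 12c = 0

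The same holds with the last wave at 18 months (c + 18c − c − 18c = 0). The rank is 3 of 4 in both cases, and none of the four coefficients is estimable on its own. Only sums such as b1 + b3, the post-implementation slope, are. More adolescents per wave make m0, m1 and m2 more precise but add no equation.

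**Step 2: a simpler model.** Dropping b3 forces one slope before and after. The design determinant at t = (−1, 6, 12) is 6 − 12 = −6, and at (−1, 6, 18) it is 6 − 18 = −12. Both are non-zero, so this model is just identified:

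- slope = (m2 − m1)/6, or (m2 − m1)/12 with the last wave at 18 months
- level change = (m1 − m0) − 7 × slope

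The slope comes wholly from the two post-implementation waves. It equals the prior trend only if the intervention did not alter the slope, and these data cannot test that.

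**Step 3: pooling the four sites.** Four site intercepts plus a common trend, level change and slope change make 7 parameters for 12 site-wave means. With the same lead time at each site the rank is 6 of 7. With lead times of 1, 2, 3 and 4 months it reaches 7, but only because trend and effects are forced to be equal across sites. The article tailors interventions to each site, so that constraint is hard to defend.

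**Step 4: illustration of the bias, on assumed trends.** The article gives no rate. A steady background trend with no intervention effect would produce these changes from a baseline at −1 month:

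| Assumed trend (SD per month) | At 6 months (× 7) | At 12 months (× 13) | At 18 months (× 19) |
|---|---|---|---|
| 0.005 | 0.035 | 0.065 | 0.095 |
| 0.01 | 0.07 | 0.13 | 0.19 |
| 0.02 | 0.14 | 0.26 | 0.38 |

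The table shows how the bias scales with trend and follow-up. It does not estimate the bias in this study.

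**The case against.** Several points on the other side have force.

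- **The wording is before, not once before.** The article condenses a fuller protocol, and the count of pre-implementation occasions is not literally stated. This stands as a caveat. One occasion is still the natural reading, and nothing in the document points to more.
- **The interrupted time series sentence covers processes as well as outcomes.** Process data are continuous and could form a real series. This stands. A reader might infer that the label fails for the whole evaluation, but the document does not support that.
- **Non-identification is not universal.** A common-slope model can be fitted. This is correct, but it borrows the prior slope from the post-implementation waves (step 2).
- **The Analyses section.** A reader might see a contradiction in its mention of "multilevel modelling appropriate for individual-level data nested within communities". That model is given only as an example and is compatible with time-series data. Leaving the segmented model unnamed is ordinary for an article, so this does not support the point.
- **Attribution does not rest on pre-post change alone.** The plan includes realist evaluation and Ripple Effects Mapping, treats age as an analysis category, and admits the lack of a control. It would go too far to say that any drift will be reported as an effect. These elements still do not replace a quantitative pre-trend, and the admitted limitation does not disclose its absence.

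**Conclusion.** The point holds for the Effects outcomes measured in waves: well-being, agency, and accelerometer and self-reported movement behaviours. For these, the label and the schedule in one paragraph do not fit together, and the claimed design strength is absent. The conclusion rests on reading the schedule as one pre-implementation occasion. It needs no assumption about variance, correlation or sample size.

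The size of the resulting bias cannot be derived from the documents. A reader might want to express it as a number of standard errors. That would require an assumed trend, an assumed pre-post correlation, a closed cohort and no variation in change between sites, and the article states none of these. Ageing acts in full only if the same adolescents are followed, which is also not stated. Other background change, such as seasonal change, would remain in either case.

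The article states no hypothesis test or power figure that depends on the label. What needs correcting is the description of the design and the strength of the conclusions drawn from it.

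**What to change.** For the wave-measured Effects outcomes:

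1. Describe the design as an uncontrolled before-after comparison with two follow-ups, and delete the statement on design strength.
2. Limit the quantitative conclusions to change over time.
3. Add to the limitations in the Discussion that no pre-implementation trend can be estimated.
4. Keep the interrupted time series label only for series with repeated pre-implementation measurements, such as the continuous process data.

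This costs wording only. The downside is a less favourable stated design strength.

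An extra pre-implementation wave is not a substitute. Two pre and two post occasions give rank 4 of 4 with no residual degrees of freedom over time points, so linearity could not be checked, and the wave would need additional resources.

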### Analyses

Data collected by adolescent-researchers throughout the co-creation process will be analysed using the best available and accessible techniques with options for facilitated co-researcher involvement. The selected methods should be engaging to the co-researchers, suited to answering their research questions and supported by a skilled academic researcher. Following data cleaning and data processing, we will analyse the outcomes of the implemented interventions, as well as the dynamics underlying these, combining and comparing data from the four study sites. We will conduct analyses of a combination of quantitative (eg, sensor-based behavioural data) as well as qualitative (eg, interviews and user-generated data) data.^83^ Quantitative data will be analysed using appropriate techniques (eg, multilevel modelling appropriate for individual-level data nested within communities). Qualitative data will be summarised and subsequently analysed using open and axial coding by two independent researchers. Intersectionality references the critical insight that race, class, gender, sexuality, ethnicity, nation, ability and age operate not as unitary, mutually exclusive entities, but as reciprocally constructing phenomena that in turn shape complex social and health inequalities.^84^ In both quantitative and qualitative analyses, we will apply different kinds of intersectional analyses including relevant categories such as gender, age, education and ethnicity.

In the social network analysis, we will focus on the relationships among relevant ‘actors’ when mapping the local setting including persons, organisations and locations to understand the inter-relations and impacts of factors at different levels—from individual-level factors to environments and policies. We will use this knowledge to identify leverage points for interventions. We will integrate realist evaluation^82^ in the process evaluation to better understand which mechanisms contributed to the observed outcomes, for example, how the achievement of individual and collective agency leads to empowerment, and under which conditions. Additionally, we will provide a tested and refined intervention theory on the application of youth-centred co-creation in vulnerable settings, focusing on social mechanisms potentially to be triggered (trust, reciprocity, neighbourhood solidarity, personal and collective agency, leadership) in a range of context conditions (typology of settings: socially cohesive long time residing migrant communities, less cohesive transient migrant communities, diverse communities, partially gentrified, etc). We will develop a plausible causal explanation, focusing also on counteracting or unintended consequences. These findings will be further synthesised into a refined intervention theory that can be used for future similar interventions and can be tested in other settings. To analyse the costs of implementation, we will use microcosting reflecting actual resource use and economic costs by collecting data on resources used and the unit costs of those resources following guidelines and checklists for conducting and reporting microcosting studies.^85^

